**Methods:**

The short-term and mid-term changes produced by different therapies on subjects with non-specific chronic neck pain will be studied. The sample will be randomly divided into three groups: manual therapy, therapeutic exercise, and placebo. As dependent variables of the study, we will take (1) Overall Balance Index, measured through a dynamic stabilometric platform; (2) pain, based on the visual analog scale and the Pressure Pain Threshold; (3) cervical disability, through the neck disability index. The findings will be analyzed statistically considering a 5% significance level (*p* ≤ 0.05).

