### Sample size calculation

The sample size was calculated using the Granmo calculator v.7.12. Based on the analysis of the variance of means, and estimating an alpha risk of 5% (0.05), a beta risk of 10% (0.10), a unilateral contrast, a typical deviation of 10% (0.10), a minimum difference to detect of 9.8% (0.098) which is based as the minimum clinically important differences in OBI [42], and a rate of follow-up losses of 15%, 10 subjects are required in each group, assuming that there are three groups. Finally, we will include 66 patients who will be divided into three groups, each group with at least 20 subjects, so as to overcome this value to assume the possible loss of follow-up.

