### Statistical analysis

The statistical analysis will be carried out using IBM-SPSS Statistics 24 software. The normality test applied to all the variables will be the Kolmogorov-Smirnov test. For the contrast of intragroup hypotheses, Student’s *t* test for paired variables will be applied in the case of parametric distributions and Kruskal-Wallis *H* for non-parametric distributions. For the intergroup hypothesis contrast, one-factor analysis of variance (ANOVA) will be used in the case of parametric distributions and Kruskal-Wallis *H* for non-parametric distributions. Post hoc analysis will be obtained through Bonferroni’s contrast for parametric distributions and Mann-Whitney’s *U* for non-parametric ones. Associations between pain (clinical improvement) and PS will be analyzed through Pearson’s *R* or Spearman’s rho. The confidence level used will be 95% (0.05), and the power of the study will be 90% (0.1).

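### A Kolmogorov-Smirnov pre-test decides whether the pairwise contrasts are Bonferroni-corrected or are Mann-Whitney tests with no stated correction, so the same comparison can face two error rules

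*Protocol article*

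**What the plan says.** All of the relevant text is in the Statistical analysis section of the protocol article.

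- Choice of branch: "The normality test applied to all the variables will be the Kolmogorov-Smirnov test".
- Three-group comparison: "one-factor analysis of variance (ANOVA) will be used in the case of parametric distributions and Kruskal-Wallis *H* for non-parametric distributions".
- Pairwise comparison: "Post hoc analysis will be obtained through Bonferroni’s contrast for parametric distributions and Mann-Whitney’s *U* for non-parametric ones".
- Level: 0.05 is the only significance level given, there and in the Abstract.

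The Abstract sets the number of arms: "The sample will be randomly divided into three groups: manual therapy, therapeutic exercise, and placebo". The Primary objective compares the two active therapies, and the Hypothesis sets the active treatments against sham. Both are pairwise questions. Under Outcome measures, OBI, VAS, PPT and NDI are each measured before treatment and at weeks 2, 4 and 12.

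The text does not say whether Mann-Whitney p-values are adjusted, or whether pairwise tests depend on a significant three-group test.

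**The concern.** The two post hoc options are different kinds of thing. Bonferroni is a multiplicity correction. Mann-Whitney U is a two-sample test with no correction built in, and none is added to it. A normality test on the trial data therefore changes two things at once: the test statistic, and the evidence required per contrast.

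The three-group test cannot answer the objective or the hypothesis; the pairwise contrasts must. The rule for declaring them positive could differ between OBI at week 4 and OBI at week 12, or between OBI and VAS, for reasons unrelated to the treatments. A family-wise error above 5% is also possible, depending on how the silent parts of the text are read.

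**Working it through.** **Inputs.** Three arms, hence three contrasts (Abstract). Level 0.05 (Statistical analysis). From Sample size calculation: difference 0.098 and SD 0.10, so 0.098/0.10 = 0.98 SD; 66 patients, so 66/3 = 22 per arm if equal, with at least 20 per arm stated. Assumptions not in the document: two-sided tests, normality tested within each arm, and lognormal data (log-SD 0.5) as the skewed case.

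**The plan's own figure.** The plan gives no family-wise error to reproduce. Its 10 per group can be reproduced by a one-way ANOVA at 90% power if the three means are assumed to lie 0.098 apart: 7.69, rounded up to 8, and 8/0.85 = 9.4, rounded up to 10. Nothing below depends on it.

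**Step 1: thresholds.** Parametric branch 0.05/3 = 0.0167 per contrast; Mann-Whitney branch 0.05. On the pooled t scale with 22 per arm (63 degrees of freedom), the smallest significant difference is t × √(2/22):
- at 0.0167: 2.460 × 0.3015 = 0.74 SD
- at 0.05: 1.998 × 0.3015 = 0.60 SD

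**Step 2: error on each branch taken alone.** For independent tests, 1 − 0.95³ = 14.3%. The three contrasts share arms, so the true figure is lower. Simulated chance of any false positive with no treatment differences (20,000 trials, 22 per arm):

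| Rule | Normal | Lognormal |
|---|---|---|
| Parametric contrasts, Bonferroni | 4.2% | 3.9% |
| Mann-Whitney at 0.05, unconditional | 12.0% | 12.2% |
| Mann-Whitney at 0.05, only after Kruskal-Wallis p < 0.05 | 4.7% | 4.9% |
| Mann-Whitney at 0.0167 | 4.2% | 4.2% |

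**Step 3: how often the branch switches.** A Lilliefors-type Kolmogorov-Smirnov test in each arm, switching if any arm rejects, sends about 13% to 15% of truly normal outcomes and about 72% to 75% of lognormal ones to the Mann-Whitney branch. Without the Lilliefors correction the figures are about 0.1% and 4%. The document does not say which version is meant. Four outcomes at three follow-up visits give 12 branch decisions if each is tested separately; with normal data and the Lilliefors version, 12 × 0.13 = 1.6 or more would be expected to switch by chance.

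**Step 4: error of the whole rule.** Simulated with the Lilliefors-type switch, 20 to 22 per arm:
- Mann-Whitney unconditional: about 5.6% (normal), about 10% to 11% (lognormal)
- Mann-Whitney only after a significant Kruskal-Wallis test: about 4.5% to 5.5% across both shapes

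For the uncorrected Kolmogorov-Smirnov version, weighting the Step 2 figures gives roughly 0.043 × 12.2% + 0.957 × 3.9% = 4.3% for lognormal data, because the switch rarely happens.

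**Step 5: power for one active-versus-sham contrast** (sham worse by 0.98 SD, 22 per arm, normal data, simulated):
- Bonferroni parametric: 77.7%
- Mann-Whitney at 0.05, unconditional: 86.7%
- Mann-Whitney at 0.05 after Kruskal-Wallis: 83.5%
- Mann-Whitney at 0.0167: 74.1%

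The two branches as written differ by 86.7 − 77.7 = 9.0 percentage points, or 83.5 − 77.7 = 5.8 if the Kruskal-Wallis condition applies.

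**The case against.** The strongest reply has three parts.

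*The missing correction is only silence.* The article condenses a fuller plan, and the adjustment of Mann-Whitney p-values is a detail an analysis plan often supplies. This stands in part: the text does not say that none will be used. But the article does more than leave multiplicity unmentioned. It fixes a rule for one branch and names a bare test for the other, and that asymmetry is in the text.

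*Post hoc implies a prior significant three-group test.* The order of the sentences suggests it, and with three arms such a condition holds the error near 5%. This stands as a reading, though the condition is never stated. On this reading no inflation is left, but the per-contrast threshold still differs between branches.

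*The 12% is not the error of the plan.* Correct. A reader might infer that the trial runs a 12% family-wise error. That figure belongs to the Mann-Whitney branch alone, run unconditionally; normal data would mostly go to ANOVA, and the whole rule then gives about 5.6%.

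A reader might also infer that, because the normality test is applied to variables and not to residuals, true treatment differences could trigger the switch. The documents do not support this. They do not say that arms are pooled for the test, and even if they were, arms shifted by the planned 0.98 SD left the rejection rate at 3% to 4%, against 3.0% with no shift.

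**Conclusion.** The point holds as an inconsistent, data-selected error rule for the pairwise contrasts. It does not hold as a demonstration that error is inflated on every reading.

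On the text as written, a contrast needs 0.0167 on one branch and 0.05 on the other. Family-wise error for the whole rule lies between about 4% and about 11%. The upper end needs all three of the following: no prior Kruskal-Wallis condition, clearly skewed data (assumed lognormal, log-SD 0.5), and a Lilliefors-type normality test in each arm. If the Kruskal-Wallis condition applies, the error is near 5% and what remains is that like comparisons are judged unlike.

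This should be settled before the data are analysed, because it governs how the main comparisons are declared positive. It does not undermine the design or the data.

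**What to change.** 1. Name one between-group analysis per outcome in advance and remove the Kolmogorov-Smirnov switch. For OBI, use ANCOVA adjusted for the baseline OBI already collected, check the residuals, and report a rank-based analysis as sensitivity.
2. State one multiplicity rule for the three pairwise contrasts that applies whichever test is used. Either use Bonferroni or Holm throughout, or test contrasts at 0.05 throughout but only after a significant three-group test. Do not mix the two across branches.

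If a non-parametric branch is kept for any outcome, the second sentence alone removes the inconsistency in the threshold.

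**Cost.** About two sentences; no change to data collection or enrolment. With Bonferroni or Holm, Mann-Whitney p-values between 0.0167 and 0.05 may no longer count. For Bonferroni at the planned effect with 22 per arm, power on that branch falls from 86.7% to 74.1% with normal data and from 95.6% to 89.2% with lognormal data; Holm loses no more than this. Requiring a significant Kruskal-Wallis test instead costs less (86.7% to 83.5% with normal data).

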### Primary objective

The aim of our study is to compare two scientifically approved therapies for NCNP—one treatment with a greater influence on the structural component, and the other one with a greater component on the central process—to observe differences in the PS of the subjects with NCNP.

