### Hypothesis

Experimental treatments have a greater beneficial effect on PS and pain of subjects with NCNP than sham treatment. The improvement in PS is linked to an improvement in the subject’s pain.

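### With exactly three groups, a written ANOVA gate followed by unadjusted pairwise tests would hold the same 5% family-wise error as the planned Bonferroni contrasts, with more power: a cheap improvement, not an error

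*Protocol article*

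**What the plan says.** The Statistical analysis section of the protocol article compares the groups by one-way ANOVA, or by Kruskal-Wallis if the data are not normal. On the parametric side it continues: "Post hoc analysis will be obtained through Bonferroni’s contrast for parametric distributions". On the non-parametric side it names Mann-Whitney and no adjustment. It does not say whether the pairwise contrasts are run only after a significant overall test. The level is 5% in that section and in the abstract ("considering a 5% significance level"); neither place says that 5% applies to each pairwise contrast.

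The pairwise contrasts carry the trial's questions. The primary objective compares the two active therapies "to observe differences in the PS of the subjects with NCNP". The hypothesis concerns each therapy against sham: "Experimental treatments have a greater beneficial effect on PS and pain of subjects with NCNP than sham treatment".

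**The concern.** Bonferroni over three contrasts is designed to work without any overall test. The plan already has an overall test, and with exactly three groups that test can carry the multiplicity control if it is used as a gate. Tightening each contrast to 1.67% then costs power without being needed to keep family-wise error at 5%. At stake is the chance of detecting differences from sham that the trial was sized to find, in a study with only about 19 to 22 patients per arm.

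**Working it through.** **Inputs.** From Sample size calculation: difference 0.098, SD 0.10, alpha 5%, beta 10%, "a unilateral contrast", 15% loss, 66 patients in three groups. From Randomization: balanced allocation, read as 22 per arm. After loss, 66 × 0.85 = 56.1, taken as 19/19/18 evaluable with sham the arm of 18.

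**The plan's own figure.** For two means, one-sided: n = 2 × (1.645 + 1.282)² × (0.10/0.098)² = 17.8, so 18 per group. Then 18/0.85 = 21.2, so 22 per group, or 66 in total. This matches the 66 but not the 10 per group also stated there. That mismatch is a separate matter; 66 is used below. The calculation makes no allowance for three contrasts.

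**Why the gate suffices.** Call the pairwise nulls MT = EX, MT = sham and EX = sham. Any two of them imply the third, so the number of true nulls is 0, 1 or 3.
- All three true: an error requires the overall test to reject, which has probability 5%.
- Exactly one true: only that one can be falsely rejected, and it is tested at 5%.
- None true: no error is possible.

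Family-wise error is therefore at most 5%. The argument fails with four or more groups.

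**Hand check, 22 per arm, contrast with sham, no gate.** Standardised difference 0.98 × √(22/2) = 3.25, with 63 df. Critical values are 2.46 (Bonferroni) and 2.00 (unadjusted).
- Bonferroni: Φ(3.25 − 2.46) = Φ(0.79), about 78%.
- Unadjusted: Φ(3.25 − 2.00) = Φ(1.25), about 89%. The gate brings this down to about 87%.

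**Simulation** (normal data, common SD, two-sided tests on the pooled error, 400,000 trials per setting). Both columns are behind a 5% ANOVA gate.

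| Setting | Evaluable | Quantity | Bonferroni | Unadjusted |
|---|---|---|---|---|
| Both therapies better than sham by 0.098 | 19/19/18 | power, each sham contrast | 69% | 79% |
| | | power, both sham contrasts | 55–56% | 73% |
| | 22/22/22 | power, each sham contrast | 78% | 87% |
| | | power, both sham contrasts | 67% | 82% |
| Sham halfway; therapies differ by 0.098 | 19/19/18 | power, manual versus exercise | 70% | 74% |
| | | power, each half-size contrast | 17% | 30% |
| | 22/22/22 | power, manual versus exercise | 78% | 81% |
| | | power, each half-size contrast | 21% | 35% |
| All groups equal | either | family-wise error | 4.2% | 5.0% |
| Two equal, third far away | either | error on the one true null | 1.7% | 5.0% |

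**If the plan intends no gate.** Bonferroni without the gate gives almost the same power: 69.4% against 69.3% (19/19/18) and 78.2% in both cases (22 per arm) for a sham contrast. For manual versus exercise with sham halfway, the gate costs at most 0.4 points. The gain from the gated rule is therefore nearly the same on either reading. Unadjusted tests with no gate have a family-wise error of about 12% when all groups are equal.

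**The case against.** Bonferroni is a valid, prespecified and common choice, and preferring a more powerful valid procedure does not make the plan wrong. That stands.

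A reader might go further and infer that testing at 1.67% contradicts the stated 5%. The documents do not support this: the protocol never promises 5% per contrast, and 0.05/3 is how 5% is kept over three contrasts. Nor are ANOVA and Bonferroni together a double penalty. The gate costs at most 0.4 points on top of Bonferroni, so the loss is the ordinary Bonferroni loss.

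The gate is not written in the protocol. The term post hoc suggests one but does not fix it. If there is none, Bonferroni is the only pairwise protection on the parametric side and cannot simply be deleted. This also stands, and it shapes the fix.

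The gain depends on the pattern of means and is small for manual versus exercise when sham lies between the therapies. Where the therapies are equal, the 1.67% level loses no power on that contrast; it only makes a false positive rarer. The 5% control also applies within one outcome at one visit. The protocol has four outcomes (OBI, VAS, PPT, NDI) at three post-baseline evaluations, and the gated rule uses the full 5% in each where Bonferroni uses somewhat less. These are fair limits, but Bonferroni over three group pairs is not a control across outcomes and visits either.

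**Conclusion.** The plan is valid as written, and the point is an inexpensive gain in efficiency. At the same 5% family-wise limit within each outcome and visit, a written gate with unadjusted contrasts adds about 9 to 10 points of power per sham contrast, and 15 to 17 points for showing both therapies better than sham, when both are better by 0.098. With sham halfway, it adds 3 to 4 points for manual versus exercise and about 13 to 14 for each half-size contrast.

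These sizes rest on the protocol's difference and SD, normal data with equal variances, two-sided tests (the Statistical analysis section does not state sidedness) and 19 to 22 evaluable patients per arm. The change does not restore 90% power for a sham contrast: 79% to 87% is still below it.

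**What to change.** In Statistical analysis, replace the Bonferroni sentence with: *Only if the overall three-group test is significant at two-sided 5% are the three pairwise contrasts tested, each at two-sided 5% (closed testing, valid because there are exactly three groups).* Write the same gate for Kruskal-Wallis followed by Mann-Whitney, so that both branches follow one rule. The gate must be explicit; dropping Bonferroni without it is not acceptable.

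The cost is one sentence, with no further patients or data. The pairwise 95% intervals would no longer be simultaneous, so Tukey intervals can be reported as a supplement. The rule must be revisited if the number of groups changes.

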### Secondary objective

A secondary objective is to analyze the evolution of cervical pain and disability according to the treatment applied and the relationship with changes produced on PS.

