### Trial design

This study is a randomized, controlled, parallel, double-blind, three-arm clinical trial of treatment.

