## Discussion

This article presents a detailed description of a randomized controlled trial designed to analyze the results in terms of pain, disability, and postural stability of two types of treatments for non-specific chronic neck pain.

We intend to investigate a little-studied field such as postural stability in these subjects and to try to understand the mechanisms that may produce these alterations. We propose two types of treatments: one using manual therapy based on the structural influences of the neck, and another based on the therapeutic exercise that exerts its effect through more neurophysiological mechanisms. By observing the effects of these two therapies, we will try to analyze and gain a better understanding of the mechanisms that cause postural instability in patients with this type of pain. Our results intend to present whether the provocative mechanisms have a more structural component, or instead are caused by alterations produced at the level of the central nervous system by its sustained exposure to pain. In addition, we intend to establish relationships between clinical improvement in relation to pain with improvement in postural stability of the subjects and to analyze the differences depending on the treatment applied.

We have designed a randomized, controlled, double-blinded clinical trial, with the aim that our study can contribute to increase scientific knowledge on this matter and initiate new lines of future research.

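### The pain-stability hypothesis is assigned a two-variable correlation with no arm term; if it is pooled over the three arms, the expected treatment effects alone can produce a correlation

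*Protocol article*

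**What the plan says.** The Hypothesis section makes two claims. The first concerns treatment effects: "Experimental treatments have a greater beneficial effect on PS and pain of subjects with NCNP than sham treatment". The second concerns an association: "The improvement in PS is linked to an improvement in the subject’s pain". The Secondary objective repeats the association, aiming "to analyze the evolution of cervical pain and disability according to the treatment applied and the relationship with changes produced on PS". The Discussion does so again: "we intend to establish relationships between clinical improvement in relation to pain with improvement in postural stability of the subjects".

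The method is one sentence in Statistical analysis: "Associations between pain (clinical improvement) and PS will be analyzed through" Pearson's R or Spearman's rho. The sentence mentions no arm covariate, stratification or partial correlation. The other comparisons in that section are labelled as within-group or between-group; this one has neither label. The Discussion adds that the investigators intend "to analyze the differences depending on the treatment applied", but attaches no method to that aim.

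**The concern.** Pearson's and Spearman's coefficients each take two variables and have no place for treatment arm. In a three-arm trial whose own hypothesis predicts that two arms will do better than the third on both variables, the arm means lie along a line. A coefficient over all 66 patients mixes that between-arm pattern with the association among patients who had the same treatment. Only the second component bears on whether those whose pain improves more also gain more stability.

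The second hypothesis could therefore be declared supported when the data show only that the treatments beat sham on two separate outcomes. The Discussion means to use this relationship in reasoning about structural versus central mechanisms, so an artefact of arm means would carry into the trial's interpretation.

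**Working it through.** The article gives no figure for the correlation, so there is none to reproduce. The check asks what a pooled coefficient would show if there were no association within arm.

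**Inputs**
- Three arms (Trial design). Randomisation is described as balanced; taken as 1:1:1.
- 66 patients (Sample size calculation): 66 / 3 = 22 per arm. With the stated 15% loss, 22 × 0.85 = 18.7, so 18 per arm is also shown.
- PS effect: planning difference 0.098 and SD 0.10 (Sample size calculation), so 0.098 / 0.10 = 0.98 SD. Assumed here to apply to change in OBI.
- Pain effect: not given for the visual analog scale or the pressure pain threshold. Assumed, range 0.3 to 0.98 SD.
- Within-arm correlation: 0 by construction. Test: two-sided, 0.05. Both outcomes coded so that positive means improvement.

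**Formula.** In within-arm SD units, let sham have mean 0 on both outcomes and both active arms have mean a on pain and b on PS. The between-arm covariance is ab × 2/9 and the between-arm variances are a² × 2/9 and b² × 2/9. With unit within-arm variances and zero within-arm covariance,

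pooled r = (2ab/9) / √[(1 + 2a²/9)(1 + 2b²/9)]

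- a = b = 0.98: 0.98² × 2/9 = 0.213; 0.213 / 1.213 = 0.176.
- a = b = 0.5: 0.25 × 2/9 = 0.0556; 0.0556 / 1.0556 = 0.053.
- a = 0.5, b = 0.98: 0.1089 / √(1.0556 × 1.2134) = 0.096.
- One therapy moving only pain and the other only PS, each by 0.98 SD: the covariance is −0.98²/9 = −0.107, so r = −0.107 / 1.213 = −0.088.

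**Simulation.** 20,000 trials per scenario, Pearson's coefficient, zero within-arm correlation. The arm-adjusted version is the partial correlation given arm, on N − 4 degrees of freedom.

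| Pain / PS effect (SD) | Pooled r, formula | Pooled false positives, 22 per arm | Pooled, 18 per arm | Arm-adjusted, 22 per arm |
|---|---|---|---|---|
| 0 / 0 | 0 | 4.9% | 4.9% | 5.0% |
| 0.3 / 0.3 | 0.020 | 5.1% | 5.2% | 4.9% |
| 0.5 / 0.5 | 0.053 | 7.1% | 6.4% | 4.9% |
| 0.5 / 0.98 | 0.096 | 12.0% | 10.6% | 5.0% |
| 0.8 / 0.8 | 0.125 | 16.9% | 14.0% | 5.2% |
| 0.98 / 0.98 | 0.176 | 29.9% | 25.6% | 5.0% |
| 0.98 / 0.98, one active arm only | 0.176 | 29.4% | 25.1% | 4.9% |
| One arm pain only, other PS only, 0.98 | −0.088 | 10.3% | 9.9% | 5.1% |

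Mean simulated r agreed with the formula to within 0.003 in every row.

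**Cross-check of the 30%.** By Fisher's transformation, atanh(0.176) = 0.178 and √(66 − 3) = 7.94, so the expected z is 1.41. The chance of exceeding 1.96 is Φ(1.41 − 1.96), about 29%, which agrees.

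**By-arm reading.** A coefficient computed inside a single arm kept its error rate (4.8% to 5.3% across the scenarios), so this reading has no such bias. It does give three coefficients on about 22 patients each. Significance then needs |r| of at least 2.086 / √(20 + 2.086²) = 0.42, and the article gives no rule for combining or comparing them.

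**The case against.** The strongest reply is that the article never says the coefficient is pooled. A Pearson coefficient within each arm fits the sentence equally well and is free of this bias, and the Discussion's intention "to analyze the differences depending on the treatment applied" points that way. A condensed article may also leave such detail to a fuller document. This stands in part: a reader might infer that the plan has chosen to ignore treatment arm, but that would be drawn from silence. The absence of a group label makes pooling a natural reading, not a stated one. Even so, the article does name a method for a stated hypothesis, and applying that method literally to the whole sample can give the wrong answer.

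The second reply is that the size depends on an assumed pain effect. This stands in full. The 0.98 SD is a minimum difference to detect in OBI, not a forecast for both arms on both outcomes, and at 0.3 to 0.5 SD the inflation is nil to slight. The two therapies were also chosen for different presumed mechanisms, so they may not move both outcomes alike. That does not remove the problem, since the bias may then run against the hypothesis.

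A reader might also infer that effective treatments would confirm the second hypothesis automatically. The figures do not support that: at 0.98 SD on both outcomes, about 70% of trials with no within-arm association remain non-significant.

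**Conclusion.** The point holds conditionally. The named method carries no arm term, and the article leaves open whether it is pooled or by arm. If pooled, it does not isolate the association that the hypothesis concerns. Its false-positive rate at 22 per arm then runs from about 5% (0.3 SD on both outcomes) through 12% (0.5 SD pain, 0.98 SD PS) to about 30% (0.98 SD on both), and the bias turns negative, r about −0.09, if each therapy acts on a different outcome.

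These figures assume equal arms, zero within-arm correlation, a two-sided 5% test, Pearson's coefficient and pain effects that the article does not supply. Spearman's rho was not simulated; it too has no arm term.

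Two stronger readings should be avoided. The contrast is between pooled and within-arm association, not within-patient association: both coefficients compare changes between patients. And the hypothesis claims a link, not that less pain causes better stability; adjusting for arm would not establish cause either. Because the bias is material at the PS effect used for planning and easily removed, the sentence should be changed before analysis.

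**What to change.** In Statistical analysis, state that the association is between change in OBI and change in pain, and that it is estimated with arm as a covariate, by a partial correlation given arm or a linear regression of OBI change on pain change with an arm term. State also that an unadjusted pooled coefficient will not serve as the test of the hypothesis.

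The cost is one or two sentences and two degrees of freedom (64 to 62 residual with 66 patients), with no new data or patients. Baseline values of both outcomes and an arm-by-change interaction are optional. They would add two degrees of freedom each, six in all with arm, and the interaction would be imprecise at about 20 per arm. If by-arm coefficients were intended, the text should say so and label comparisons between them as descriptive.

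### The stated 90% power rests on a one-sided contrast and does not hold for the planned ANOVA and Bonferroni contrasts: after 15% losses, 66 patients give about 68% to 70% for a pairwise contrast and 74% to 86% for the ANOVA

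*Protocol article*

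**What the plan says.** The Sample size calculation section names analysis of variance as its basis. It sets "estimating an alpha risk of 5% (0.05" and "a beta risk of 10% (0.10", and then "a unilateral contrast, a typical deviation of 10% (0.10), a minimum difference to detect of 9.8% (0.098". With 15% follow-up losses it arrives at a requirement of 10 per group. It then plans to enrol 66, with at least 20 in each of the three groups.

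The Statistical analysis section says "For the intergroup hypothesis contrast, one-factor analysis of variance (ANOVA) will be used in the case of parametric distributions", with Bonferroni contrasts as the post hoc step. It closes with "The confidence level used will be 95% (0.05), and the power of the study will be 90% (0.1".

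The Primary objective compares the two active therapies "to observe differences in the PS of the subjects with NCNP" and gives no direction. The Hypothesis section is directional, but only for the experimental treatments against sham.

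**The concern.** Sidedness, test, multiplicity adjustment and power are all stated in the protocol, and they do not fit together. An F test across three groups cannot be one-sided. A Bonferroni contrast over three pairs is judged at 0.05/3, not at 0.05. No single unadjusted one-sided comparison between groups is planned anywhere.

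The comparison of the two therapies matters most here, because the Discussion section intends to reason from how they differ to a structural or a central mechanism. If the type II error for that comparison is about 30% and not 10%, a non-significant result carries much less information than a stated power of 90% suggests.

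**Working it through.** **Inputs.** From the Sample size calculation: difference 0.098, SD 0.10 (standardised difference 0.98), alpha 0.05, beta 0.10, one-sided, 15% losses, 66 patients. Equal allocation gives 22 per group, or 22 × 0.85 = 18.7 after losses. From the Statistical analysis: one-way ANOVA at 0.05, then Bonferroni contrasts. I assume three pairs, tested two-sided at 0.05/3 = 0.0167.

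**The plan's own figure.** For a one-sided, unadjusted comparison of two groups by the normal approximation:

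n = 2 × (1.645 + 1.282)² / 0.98² = 17.8, so 18 per group; 18/0.85 = 21.2, so 22 per group; 3 × 22 = 66.

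This matches the enrolment, and at 18.7 per group that test has 90% power by the noncentral t. The protocol does not say that 66 was derived this way. It attaches the calculation to 10 per group, which this formula does not give.

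**Power of the planned tests.**

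- Pairwise: noncentral t with noncentrality 0.98 × √(n/2), which is 2.19 at n = 10, 3.00 at n = 18.7 and 3.25 at n = 22. Ranges in the table come from using two-group or pooled three-group degrees of freedom.
- ANOVA: noncentral F with λ = n × Σ(μᵢ − mean)² / SD².
  - Third mean midway (0, 0.049, 0.098): Σ = 2 × 0.049² = 0.004802, so λ = 8.98 at n = 18.7.
  - Both active arms 0.098 from sham: Σ = (2/3) × 0.098² = 0.006403, so λ = 11.97 at n = 18.7.

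| Test | 10 per group | 18.7 per group (15% lost) | 22 per group (none lost) |
|---|---|---|---|
| One-sided 0.05, unadjusted pair | 68% | 90% | 94% |
| Two-sided 0.05, unadjusted pair | 55–56% | 83–84% | 89% |
| Two-sided 0.0167, Bonferroni pair | 35–38% | 68–70% | 77–78% |
| ANOVA, third mean midway | 44% | 74% | 82% |
| ANOVA, both active arms 0.098 from sham | 56% | 86% | 92% |

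**Where the pairwise power goes.** At 18.7 per group, moving from one-sided to two-sided costs 6 to 7 points (90% to 83–84%). The Bonferroni adjustment then costs about 14 more (to 68–70%). Multiplicity is the larger part and sidedness the smaller.

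**The case against.** Several points on the other side are fair.

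- **ANOVA is named in the sizing.** It is therefore too firm to say that the calculation belongs wholly to another test. What the text shows is an ANOVA basis joined to "a unilateral contrast", and those two do not go together.
- **The Hypothesis is directional against sham.** A one-sided basis is arguable for that comparison, but not for therapy against therapy. Direction would not restore 90% in any case: a one-sided contrast at 0.0167 has 78% to 79% at 18.7 per group.
- **The 90% is formally attached to 10 per group, with 66 chosen to exceed it.** That is so, but 10 per group falls short of 90% under every test in the table.

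A reader might also infer stronger claims, which the documents do not support.

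- *That 66 patients simply give 70% to 75% power.* This range needs the 15% losses and, for the ANOVA, the least favourable mean pattern.
- *That only a one-sided unadjusted test can reach 90%.* With no losses and both active arms 0.098 from sham, a pattern that fits the Hypothesis, the ANOVA reaches 92%. That does not help the primary comparison, because the F test does not say which arms differ, and the Bonferroni contrast between the therapies stays at 77% to 78%.
- *That the investigators will read a null result as equivalence.* No passage says so. The risk lies in how the stated power may be used.

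**Conclusion.** Wrong as written. Neither the stated 10 per group nor, after the protocol's own losses, the planned 66 patients give 90% power for the planned tests. For the therapy-against-therapy contrast, power is about 70% after 15% losses and below 80% with none, so its type II error is about three times the stated 10%. The ANOVA result depends on the mean pattern: 74% to 86% after losses, 82% to 92% without.

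These figures take the protocol's difference and SD at face value and assume normal data, equal groups and three two-sided Bonferroni comparisons. They show that the power claim is misstated. They do not show that the test, the estimate or the error control is invalid, or that enrolment has to rise.

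**What to change.** **Sample size calculation.** Delete the word that makes the contrast one-sided. Remove the statement that 10 per group are required at a beta risk of 10%; if it stays, the section contradicts the new figures. State the power that 66 patients give for the planned tests, with the conditions named: after 15% losses, about 74% for the ANOVA with the third mean midway, 86% with both active arms 0.098 from sham, and 68% to 70% for a Bonferroni contrast; with no losses, 82%, 92% and 77% to 78%.

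**Statistical analysis.** Replace "the power of the study will be 90% (0.1" with the same figures, giving about 70% after 15% losses for the Bonferroni contrast between the two therapies.

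**If a baseline-adjusted analysis is adopted.** State its power over a range of baseline correlations and label the correlation as an assumption, because the protocol gives none. With the residual SD taken as 0.10 × √(1 − r²) and 18.7 per group, ANOVA (midway) and Bonferroni power are about 79% and 75% at r = 0.3, 86% and 83% at r = 0.5, and 96% and 95% at r = 0.7.

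**Cost.** A few sentences in two sections, and a less favourable stated power. No extra patients, and no change to treatment or visits.
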